### Project 2. Assessment of response to vaccinations under treatment with IMP compared to SOC

Recently, mTOR inhibitors have been shown to enhance immune function and the response to vaccination (e.g. the influenza vaccine) at doses that were relatively well tolerated in the elderly [55, 56]. The impact of mTOR inhibitors on basic immunization in children has been insufficiently studied. Measurement of vaccination titers in the treatment group compared to the control group will assess differences in vaccination response and immunization. For this purpose, the titers of vaccines applied during the first year (measles, mumps, rubella, tetanus, pertussis, varicella; hepatitis b, polio) will be assessed in both groups.

To allow a detailed analysis of our cohort, standardized sample collection will be done longitudinally at two timepoints:

- Visit 8 (12 months of age) and Visit 12 (24 months of age).

### Project 3. Long-term developmental outcome at 60 months of age

As part of a long-term longitudinal follow-up assessment of study results, a follow-up survey of developmental status and indicators of the presence of autism spectrum disorder will be collected at 60 months of age (5 years) measured by the Vineland Adaptive Behaviour Scales (VABS-3; digital), the Social Communication Questionnaire (SCQ) and the TAND-L Checklist (German version). This aims at investigating the long-term effect of the study medication beyond the treatment period. In addition, signs of autism spectrum disorder can be detected at this age with a higher diagnostic certainty. By comparing subsequent outcomes to the study data from the 24-month assessment, potential predictors for long-term outcome will be identified. In addition, the impact on quality of life will be stratified based on data on the severity of TSC impairment (cognitive development, seizure burden, autism spectrum disorder) and measured by the quality of life in childhood epilepsy (QOLCE; caregiver-report for aged 2- < 11) [57]. As part of the consent for this accompanying study, guardians are asked for their consent to store their contact details until the time of the follow-up survey.

|                                                                    |                                              |                                |
|--------------------------------------------------------------------|----------------------------------------------|--------------------------------|
| Clinical Trial Code: PROTECT
EU trial number: 2022-502332-39-00 | Trial Protocol
(Version 06; (01.10.2024)) | Page 38 of 110
CONFIDENTIAL |
|--------------------------------------------------------------------|----------------------------------------------|--------------------------------|

### 3. Clinical Trial Design

#### 3.1 Overall Trial Design

The clinical trial is planned as a two-armed, randomized, observer-blind, controlled phase IIb clinical trial for children <4 months of age at inclusion.

The treatment group will receive daily oral mTOR inhibitor (sirolimus) therapy in addition to standard of care (SOC), starting within the first 4 months of life. Sirolimus will be continued until the 2nd birthday when neuropsychologic testing will be done. The control group will receive SOC treatment only. Patients randomized to the treatment group will be followed closely with mandatory study visits at screening, start of treatment (V1), titration visits V2-V4 and at an age of 3, 6, 9, 12, 15, 18, 21 and 24 months for safety measures, to adjust sirolimus dosages following PK testing according to prespecified algorithms and to ensure compliance. In case neonates receive their first dose of IMP under the age of 4 weeks (corrected gestational age <4 weeks of life), caregivers will have up to two additional telephone calls by the study personnel up to the end of the 4th week of life. These calls will take place in those weeks where no titration visit takes place. An end-of-trial visit at 25 months of age will monitor safety parameters after end of trial. Subjects randomized to the control group will be treated according to SOC. No placebo will be administered to reduce the number of laboratory examinations at screening, 6 months, 12 months, and 24 months of age to the minimum required to control for laboratory abnormalities unrelated to the study intervention. Mandatory study visits for the control group are at screening and at 3, 6, 9, 12, 15, 18, 21 and 24 months of age. The enrolment in the primary study ends with the end-of-trial visit at age 25 months. Therapy of TSC manifestations according to SOC in both groups will not be affected by the trial. Seizure diaries, use of anti-seizure medications and concomitant medications, adverse events, vital signs (blood pressure, temperature, heart rate), height, body weight, OFC, and physical / neurological exam, and developmental milestones will be assessed at every visit. EEG and abdominal sonography will be done as described in chapter 6. Neuropsychologic testing will be performed at 12 and 24 months of age.

A schematic of the trial design is shown:

Figure 3: Schematic diagram of trial

[figure not shown]

|                                                                    |                                              |                                |
|--------------------------------------------------------------------|----------------------------------------------|--------------------------------|
| Clinical Trial Code: PROTECT
EU trial number: 2022-502332-39-00 | Trial Protocol
(Version 06; (01.10.2024)) | Page 40 of 110
CONFIDENTIAL |
|--------------------------------------------------------------------|----------------------------------------------|--------------------------------|

### 3.2 Overall Duration of the Trial

The duration of the clinical trial for each subject is scheduled to be 21-25 months, depending on the time of enrolment in the study (0 to <4 months of age), including a treatment phase until 24 months of age and a one-month follow-up.

The overall duration of the clinical trial is expected to be 82 months. Recruitment of subjects will start in Q2 2023. The actual overall and/or recruitment duration may vary. An initial safety analysis after titration phase (V4) of 5 patients in the treatment group will be done. The clinical trial end is defined as LSLV (last subject last visit).

|                                 |           |
|---------------------------------|-----------|
| Total clinical trial duration:  | 82 months |
| Duration of the clinical phase: | 67 months |
| FSI (First Subject In):         | Q1 2024   |
| LSLV (Last Subject Last Visit): | Q2 2029   |
| DBL (Data Base Lock):           | Q2 2029   |
| Statistical analysis completed: | Q3 2029   |
| Reporting                       | Q4 2029   |

### 3.3 Duration of Trial Participation for each Subject

The trial consists of:

- a 2-week screening period
- a 21-24-month treatment period
- a 1-month post treatment follow-up period

In total the duration of the clinical trial for each subject is expected to be 21-25 months.

### 3.4 Interim Analysis

No interim analysis is planned.

### 3.5 Determination of End of Trial (all subjects)

The clinical trial end is defined as “last subject last visit” (LSLV).

In case of an early termination of the trial (see chapter 7.6), the date of the early termination will be the date of the end of trial.

### 3.6 Patient Involvement

Early-on involvement of patients in this study will improve participants’ experience in clinical trials, increase recruitment, reduce upfront protocol amendments and dropout rates and ensure investigation and communication of most important treatment benefits. During the clinically active trial, structured surveys (i.e., feedback questionnaires) and spontaneous reports of the study participants will help to decrease challenges and improve study performance. At the end of the study the patients/patient advocates are encouraged to support the dissemination of its results among patients and patient groups. The patient organization “*Tuberöse Sklerose Deutschland e.V.*” (TSD), has been involved in the planning of this study from the beginning. Prior to planning, the outline of this study has been discussed during a German wide TSD meeting with TSC

|                                                                    |                                              |                                |
|--------------------------------------------------------------------|----------------------------------------------|--------------------------------|
| Clinical Trial Code: PROTECT
EU trial number: 2022-502332-39-00 | Trial Protocol
(Version 06; (01.10.2024)) | Page 41 of 110
CONFIDENTIAL |
|--------------------------------------------------------------------|----------------------------------------------|--------------------------------|

specialists, caregivers of affected patients and patient advocates. During the preparation of this proposal, regular meetings and discussions with the TSD have taken place and adjustments to the protocol have been made according to the recommendations of the scientific committee of the TSD, patient advocates and German TS clinics. Recently, the TSD awarded us with the “*TSC-Forschungspreis*” honoring our previous contribution to the field and supporting our prospective efforts regarding mTOR inhibitor treatment in children with TSC. In addition, the patient organization “*Allianz Chronischer Seltener Erkrankungen e.V.*” (*Achse e.V.*) announced their support for our trial and committed to regular involvement in further planning. See Appendix A, letters of endorsement of the *TSD* and *Achse e.V.*.

|                                                                    |                                              |                                |
|--------------------------------------------------------------------|----------------------------------------------|--------------------------------|
| Clinical Trial Code: PROTECT
EU trial number: 2022-502332-39-00 | Trial Protocol
(Version 06; (01.10.2024)) | Page 42 of 110
CONFIDENTIAL |
|--------------------------------------------------------------------|----------------------------------------------|--------------------------------|

## 4. Subject Selection

### 4.1 Number of Subjects and Sites

A total of 60 subjects will be enrolled in the clinical trial, i.e. 30 subjects per treatment group (see chapter 9.9).

The clinical trial will be multicenter study.

It is intended that the clinical trial will take place at approximately 17-20 sites.

To ensure the best possible distribution, the study has been announced on a German wide TSC meeting in February 2021. Subsequently, 16 German centres have declared their support in participating in the trial. To achieve the recruitment goal, the most promising centres were selected during pre-study visits. German-speaking centres in Austria and Switzerland were also included in the evaluation. All German TSC centres and associated clinics have announced their support in recruiting and / or referring patients to study centres.

If enrolment is delayed, additional sites may be recruited. Screening of subjects for this trial is competitive, i.e. screening for the trial will stop at all sites at the same time once a sufficient number of subjects has been included into the study. Investigators will be notified about screening completion and will then not be allowed to screen additional subjects. Subjects already in screening at this time will be allowed to continue to randomization if eligible.

If an insufficient number of study participants have been enrolled to meet the clinical endpoint, an extension of the enrolment period may occur.

### 4.2 General Criteria for Subject Selection

Children with at least 39 weeks of corrected gestational age until the age of <4 months, with a definite diagnosis of TSC according to the 2021 Updated International Tuberous Sclerosis Complex Diagnostic Criteria are eligible for the study [58]. A history of significant prematurity, defined as gestational age <30 weeks at the time of delivery, or other significant medical complications at birth or during the neonatal period that, apart from TSC, would convey additional risk of seizures or neurodevelopmental delay (i.e. HIE (Hypoxic Ischemic Encephalopathy), severe neonatal infection, major surgery, prolonged ventilatory or other life-saving supportive care or procedures) are excluded.

As there will be no preferences on the selection of sexes to be included, it is anticipated that the clinical trial results will give a representative sex distribution, which should reflect the natural distribution in the underlying disease.

The EPISTOP trial can be considered as a broadly comparable study, however in a European setting as detailed above (6). Considering the incidence of TSC (1:6,760 – 1:13,520 live births) in Germany and the multicenter study design, a recruitment period of 3.5 years was calculated as sufficient to answer our research question.

Children with TSC are usually not born completely healthy, but in the majority of cases show clinical signs prenatally or shortly after birth. A recent prospective epidemiologic study on 86 TSC patients in Germany, aimed at determining the incidence and diagnostic delay of TSC, reports that diagnosis is oftentimes suspected in the prenatal stage due to cardiac rhabdomyomas detected on gestational ultrasounds (22.1%), or shortly after birth due to central nervous system involvement (73.3%). Median age at possible or definite diagnosis was, thereby, reported as 6 months (range: 5 months prior to birth to 16.4 years of age) [2]. An even earlier diagnosis was reported in 2017 by Davis *et al.*, who conducted a prospective study aimed at evaluating the presentation and diagnosis of TSC in infants from 5 centers in the United States. The study analyzed data of 130 infants with TSC and found that 35% presented prenatally and 41% at birth

|                                                                    |                                              |                                |
|--------------------------------------------------------------------|----------------------------------------------|--------------------------------|
| Clinical Trial Code: PROTECT
EU trial number: 2022-502332-39-00 | Trial Protocol
(Version 06; (01.10.2024)) | Page 43 of 110
CONFIDENTIAL |
|--------------------------------------------------------------------|----------------------------------------------|--------------------------------|

or within the first month of life, calculating the median time of presentation to be at birth. 74% met criteria for a definite TSC diagnosis at or within 30 days of presentation (median age at diagnosis 32 days) [30]. Thus, TSC is in most cases suspected around birth and confirmed shortly after.

### 4.3 Inclusion Criteria

Subjects meeting all of the following criteria will be considered for admission to the clinical trial:

1. Definite diagnosis of TSC according to the 2021 Updated International Tuberous Sclerosis Complex Diagnostic Criteria [58].
2. <4 months of age at the time of enrolment (randomization and treatment initiation must occur before 4 months of age; infants born prematurely must have a corrected age of at least 39 weeks, calculated by subtracting the number of weeks born before 40 weeks gestation from the actual chronological age, in weeks).
3. Signed informed consent from legal guardian(s) prior to any study specific procedure.

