### 4.4 Exclusion Criteria

Subjects presenting with any of the following criteria will not be included in the clinical trial:

1. Has a TSC-associated condition for which mTOR treatment is clinically indicated (i.e. SEGA).
2. Has been treated in the past or is currently being treated at the time of enrolment with systemic mTOR inhibitors (such as rapamycin, sirolimus, or everolimus).
3. Contraindication to study medication. Rapamune® oral solution contains soya oil. Patients allergic to peanut or soya must not take this medicine.
4. Current enrolment, or observation period of competing clinical trials at any time during enrolment in the study.
5. Has a history of significant prematurity, defined as gestational age <30 weeks at the time of delivery, or other significant medical complications at birth or during the neonatal period that other than TSC would convey additional risk of seizures or neurodevelopmental delay (i.e. HIE, severe neonatal infection, major surgery, prolonged ventilatory or other life-saving supportive care or procedures).
6. Abnormal laboratory values at screening (i.e., renal function, liver function, or bone marrow production) that are in the opinion of the investigator clinically significant and may jeopardize the safety of the study patient.
7. Parents / caregivers who are, in the opinion of the investigator, unable to comply with the requirements of the study.

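### As written, no premature infant can meet inclusion criterion 2: its corrected-age formula stays below 17.6 weeks before 4 months of age, against a threshold of 39 weeks

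*Protocol*

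**What the plan says.** Section 4.3, criterion 2, sets an upper age limit for every participant: "<4 months of age at the time of enrolment (randomization and treatment initiation must occur before 4 months of age". For one group it adds a lower limit: "infants born prematurely must have a corrected age of at least 39 weeks". The same sentence defines that quantity: "calculated by subtracting the number of weeks born before 40 weeks gestation from the actual chronological age, in weeks". The synopsis repeats the whole criterion, including the requirement of a "corrected age of at least 39 weeks, calculated by subtracting the number of weeks born before 40 weeks gestation" from chronological age.

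Section 4.2 gives the same 39 weeks under a different name and without a formula: "Children with at least 39 weeks of corrected gestational age until the age of <4 months".

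Exclusion criterion 5 in section 4.4 sets the lower limit on gestation at birth: "Has a history of significant prematurity, defined as gestational age <30 weeks at the time of delivery". Birth at 30 weeks or later is not a reason for exclusion on grounds of prematurity.

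The term *corrected gestational age* also appears in the neonatal footnote to the Schedule of Assessments and in sections 3.1, 5.2.2.7 and 6.4. There it is compared with 4 weeks of life, to identify the neonates whose caregivers receive additional telephone calls.

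**The concern.** The two conditions in criterion 2 appear to exclude each other for the group that the second condition addresses. Age counted from birth and then reduced for prematurity is a small number of weeks in a child under 4 months. A threshold of 39 weeks belongs to a scale that starts at gestation.

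Eligibility has to be reviewed and documented before randomization (section 5.1.1), and a child may be randomized when all criteria are met (section 6.8). A site that follows the text must screen-fail every premature infant. A site that follows what it takes to be the intention enrols a child who fails a written inclusion criterion. With about 17 to 20 sites planned (section 4.1), both practices can occur in the same trial.

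**Working it through.** **Inputs**

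- Upper age limit: under 4 months (section 4.3). In weeks this is 4 × 30.4375 / 7 = 17.39 on average, 123 / 7 = 17.57 for the longest run of four calendar months, and 16 if a month is taken as 4 weeks.
- Threshold: at least 39 weeks (section 4.3).
- Written formula: corrected age = chronological age − (40 − GA), where GA is gestational age at birth in weeks (section 4.3).
- Lowest GA not excluded: 30 weeks (section 4.4).
- The Protocol does not state the GA below which an infant counts as premature. I show 36+6 weeks as the conventional upper end. The conclusion does not depend on it.

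**Can the written formula reach 39?** The column of highest values takes age 17.39 weeks, for example 17.39 − (40 − 30) = 7.39. The next column solves age − (40 − GA) = 39, so age = 79 − GA. The last column is for comparison: on a scale of GA plus chronological age, 39 is reached at age 39 − GA.

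| GA at birth | Highest value before 4 months, written formula | Age at which the written formula gives 39 | Age at which GA + age gives 39 |
|---|---|---|---|
| 30 | 7.39 | 49.0 wk (11.3 months) | 9.0 wk |
| 32 | 9.39 | 47.0 wk (10.8 months) | 7.0 wk |
| 34 | 11.39 | 45.0 wk (10.3 months) | 5.0 wk |
| 36 | 13.39 | 43.0 wk (9.9 months) | 3.0 wk |
| 36+6 | 14.25 | 42.1 wk (9.7 months) | 2.1 wk |

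For birth at 36+6, the highest value is 14.43 with 17.57 weeks and 12.86 with 16 weeks. In general, for any GA below 40 the formula gives less than chronological age, hence less than 17.57. No month-to-week conversion changes this. Reading the 4-month limit itself as corrected age does not help either, because corrected age would then be under 17.57 weeks by definition.

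**Where the 39 fits.** The difference between the two scales is (GA + age) − [age − (40 − GA)] = 40 weeks for every child. Born at 32 weeks and aged 8 weeks, a child scores 8 − 8 = 0 on the written formula and 32 + 8 = 40 on the gestational scale. Born at 34 weeks and aged 8 weeks, the values are 8 − 6 = 2 and 34 + 8 = 42. The threshold can be met on the gestational scale and not on the written one.

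**The term elsewhere.** If *corrected gestational age* meant GA plus chronological age throughout, the under-4-weeks condition in sections 3.1, 5.2.2.7 and 6.4 and in the Schedule footnote could never apply, because every infant not excluded for prematurity is at 30 weeks or more on that scale from birth. If it meant weeks of life throughout, the 39 weeks in section 4.2 could not be reached before 4 months. The Protocol therefore uses one term on two scales.

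**The case against.** The arithmetic is not open to dispute, and no other section corrects it. The fair objections concern its consequences, and four inferences that a reader might draw go too far.

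- *All premature infants will be excluded in practice.* Section 4.2 and the 30-week limit in section 4.4 make the intention to admit some premature infants recognisable, and many sites will probably apply a gestational reading. This stands: the likely harm is inconsistency and formal deviations, not certain exclusion.
- *The eCRF will reject these infants.* The Protocol does not say that the formula is programmed. Section 5.1.1 describes staff review, data entry and an unspecified internal validation. Sections 5.4 and 5.5 describe an eCRF calculation only for the starting dose.
- *Recruitment will suffer.* The Protocol gives no proportion of infants with this disease born prematurely at 30 weeks or later, and section 9.9 regards randomizing 60 patients as feasible. No loss can be stated.
- *Section 4.2 settles the formula.* It contains no formula, and four other places use its term on a weeks-of-life scale. It suggests the gestational reading but does not establish it.

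The effect on the analysis is also limited. Section 9.1 puts all randomized patients in the FAS and the safety set. Its eligibility conditions for the PPS are inclusion criterion 1 and exclusion criteria 1 and 2, not inclusion criterion 2. Under section 7.2, an unmet criterion found after inclusion leads to permanent discontinuation of the study drug only if the investigator sees a risk in continuing. How such a deviation is graded is left to a separate plan (section 13.6).

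None of this makes the criterion satisfiable.

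**Conclusion.** Criterion 2 is wrong as written, in section 4.3 and in the synopsis. The written formula falls short of 39 by at least 39 − 17.57 = 21.4 weeks for any infant born before 40 weeks, and by about 24.7 weeks (39 − 14.25) or more for birth at 36+6 or earlier with an average month. The only inputs are the Protocol's own age limit, threshold and formula, so the finding rests on no outside figure. The month-to-week conversion and the definition of prematurity do not affect it.

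The cause appears to be two scales set 40 weeks apart. That the 39 weeks is meant on the gestational scale is the likely reading, but it is an inference. What follows is a risk of differing eligibility decisions between sites and of avoidable deviations, in a number of infants that the Protocol does not let one estimate. The documents do not support a claim of lost recruitment, of a faulty eCRF check or of damage to the FAS or PPS.

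**What to change.** The sponsor should:

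1. State which scale the 39 weeks refers to, and make the threshold and the formula agree in section 4.3, section 4.2 and the synopsis.
2. Define *corrected age* and *corrected gestational age* once, and use them consistently in the Schedule of Assessments footnote and in sections 3.1, 5.2.2.7 and 6.4.
3. Align any eCRF eligibility check with the reconciled wording, if such a check exists.

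The criterion governs how early a premature infant may enter and receive study drug, and section 5.2.2.7 discusses excipient exposure in neonates. The choice of scale and threshold is therefore the sponsor's clinical decision. This review asks only that the passages be reconciled.

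The cost is small: one clause in the next amendment, carried into three places, the terminology in four others, and an edit check where there is one. The sample size, the randomization and the analysis are unaffected.
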